## Abstract

**Background:** Preventing and/or reducing acute lower respiratory infections (ALRIs) in young children will lead to substantial short and long-term clinical benefits. While immunisation with pneumococcal conjugate vaccines (PCV) reduces paediatric ALRIs, its efficacy for reducing infant ALRIs following maternal immunisation has not been studied. Compared to other PCVs, the 10-valent pneumococcal-*Haemophilus influenzae* Protein D conjugate vaccine (PHiD-CV) is unique as it includes target antigens from two common lower airway pathogens, pneumococcal capsular polysaccharides and protein D, which is a conserved *H. influenzae* outer membrane lipoprotein.

**Aims:** The primary aim of this randomised controlled trial (RCT) is to determine whether vaccinating pregnant women with PHiD-CV (compared to controls) reduces ALRIs in their infants' first year of life. Our secondary aims are to evaluate the impact of maternal PHiD-CV vaccination on different ALRI definitions and, in a subgroup, the infants' nasopharyngeal carriage of pneumococci and *H. influenzae*, and their immune responses to pneumococcal vaccine type serotypes and protein D.

**Methods:** We are undertaking a parallel, multicentre, superiority RCT (1:1 allocation) at four sites across two countries (Australia, Malaysia). Healthy pregnant Australian First Nation or Malaysian women aged 17–40 years with singleton pregnancies between 27^+6^ and 34^+6^ weeks gestation are randomly assigned to receive either a single dose of PHiD-CV or usual care. Treatment allocation is concealed. Study outcome assessors are blinded to treatment arms. Our primary outcome is the rate of medically attended ALRIs by 12-months of age. Blood and nasopharyngeal swabs are collected from infants at birth, and at ages 6- and 12-months (in a subset). Our planned sample size (*n* = 292) provides 88% power (includes 10% anticipated loss to follow-up).

**Discussion:** Results from this RCT potentially leads to prevention of early and recurrent ALRIs and thus preservation of lung health during the infant's vulnerable period when lung growth is maximum. The multicentre nature of our study increases the generalisability of its future findings and is complemented by assessing the microbiological and immunological outcomes in a subset of infants.

**Clinical Trial Registration:**
https://www.anzctr.org.au/Trial/Registration/TrialReview.aspx?id=374381, identifier: ACTRN12618000150246.

## Introduction

The global burden of disease study estimated that acute lower respiratory infections (ALRIs) caused 2.74 million [95% uncertainty interval (UI) 2.50–2.86 million] deaths in 2015 with much of the burden borne by children aged <5-years [704,000 deaths (95% UI 651,000–763,000)] living in low-middle income countries (LMICs) (1). The global morbidity of ALRIs is also high (~120 million episodes in children aged <5-years) in both LMICs and high-income countries (2). In the United States (US), ALRIs are the leading cause of hospitalisation during infancy (2). Furthermore, the highest published rates of hospitalised ALRI and radiographically-confirmed pneumonia in children aged <5-years are in First Nations people living in high-income countries. In the Northern Territory of Australia, where childhood vaccine uptake is high, the incidence rate of hospitalised ALRI in First Nations children in the first year of life is 427 episodes per 1000 child-years [95% confidence interval (CI) 416–437], while in Central Australia incidence rates for radiographically-confirmed pneumonia are 27 per 1,000 child-years (95% CI 25–28) in those aged <5-years and 78.4 per 1,000 child-years (95% CI 68–90) in those <1-year of age (3).

Whilst the global mortality of childhood ALRIs has declined (1), morbidity and long-term outcomes of ALRIs remain an important public health issue. ALRIs risk injuring the developing lung, which may lead to subsequent impaired lung growth and function (4, 5) and predispose children to chronic lung disease (6). Our previous international cohort (7) study found that early-onset ALRI requiring hospitalisation (first episode occurred at median age of 3.7-months) was an independent risk factor for bronchiectasis. Similarly, First Nations children hospitalised with ALRI previously were 15-times more likely than controls (First Nations children hospitalised for other reasons) to develop bronchiectasis [odds ratio (OR) 15, 95% CI 4–53] and the risk increased further in those with recurrent ALRI episodes (8).

It is being appreciated increasingly that ALRIs early in life are associated with lung function deficits in older children and adults and also with chronic respiratory illnesses (4, 5), especially chronic obstructive pulmonary disease (COPD). ALRIs in the first 2-years of life are significantly associated with COPD (9) and non-smoking related COPD is now recognised as a major global health problem (9, 10). Both bronchiectasis and COPD are common among disadvantaged “at-risk populations” encountered in LMICs (11) and amongst First Nations populations (12). Thus, intervention strategies that reduce infant ALRIs, especially in “at-risk populations” will likely have both immediate and large long-term benefits.

One strategy to reduce infant ALRIs is maternal immunisation. Physiological and immunological changes during pregnancy result in an increased infection risk for both the mother and foetus (13). Maternal immunisation could protect the mother against infection and its adverse consequences for the foetus and also provide passive protection against infection in the first months of life for the newborn infant (14). Transfer of maternal immunoglobulin (Ig) G starts from the second trimester (15) but the most active transplacental transport of maternal immunoglobulin (Ig) G occurs after 32-weeks gestation (14). Hence immunising pregnant woman between 28 and 32-weeks (a robust IgG response takes ~4-weeks) is the ideal timing to maximise transplacental transfer of vaccine-specific IgG for passive infant protection prior to priming from vaccines initiated in early infancy (14).

Maternal immunisation is a rapidly developing field offering tremendous large-scale benefits for mothers and infants (16–18). Recognising the potential of maternal immunisation as a prevention strategy, the US National Institute of Health sponsored a series of meetings toward its development (16). The Global Alignment of Immunisation Safety Assessment in pregnancy (GAIA) consortium was also formed and published a series of papers to standardise methodology and definitions (19). Current US (18) and Australian (20) guidelines recommend both the combination diphtheria-tetanus-acellular pertussis (dTaP) and seasonal influenza vaccines for all pregnant women as there is proven efficacy of their positive impact. Although pneumococcal vaccines during pregnancy are recommended when selected risk factors are present in the mother, there are insufficient data to offer routine pneumococcal vaccination for all pregnant women (18, 20). Neonatal vaccination is an alternative strategy, but is inferior to maternal immunisation as newborn infants have limited Th1 responses to many vaccine antigens (14, 21). Thus, unlike maternal immunisation, neonatal immunisation with pneumococcal vaccines does not reliably provide sufficient protection during the first weeks of life (22), although reassuringly does not appear to induce immune tolerance.

Many pathogens cause ALRI in young children. Globally, *Streptococcus pneumoniae* (pneumococci) is reported to be the largest contributor to deaths annually from ALRIs in all age groups [55.4% or 1.52 million (95% UI 858,000–2.18 million)], including children <5-years of age [55.8% or 393,000 (95%UI 228,000–532,000)] (1). Also, pneumococci remain the most common cause of community-acquired pneumonia in adults (23). Unsurprisingly, pneumococcal infection was one of the most common ALRIs in high-income countries before pneumococcal conjugate vaccines (PCV) were introduced (24). As Australian First Nations children and adults have an increased risk of ALRI and pneumococcal infection, they have a different immunisation schedule to other Australians (20) and had PCVs several years earlier than other community groups (3, 25). Currently, Northern Territory First Nations children receive a 13-valent PCV (PCV-13 or Prevenar-13) at 2, 4 and 6-months of age as their primary course and a booster dose at age 12-months (3 + 1 schedule), while all adults aged ≥50-years receive PCV-13 followed by two doses of the 23-valent pneumococcal polysaccharide vaccine (PPV-23) 5-years apart (20). In contrast, the national immunisation program schedule for other Australians is two doses of PCV-13 at 2 and 4-months of age with a booster at 12-months (2 + 1 schedule) and a single dose of PCV-13 at age 70-years (20). Thus, the potential beneficial effects of protecting the infant against pneumococcal infections align with the data supporting a maternal immunisation strategy to reduce ALRIs, especially for First Nations infants.

There are several licenced pneumococcal vaccines, the old PPV-23 and newer PCVs. Unlike the plain polysaccharide vaccines, the protein-conjugated PCVs are T-cell dependent and capable of inducing immunity in infants, resulting in high-affinity antibodies with isotype switching, affinity maturation and generation of immunological memory. The PCVs vary in their number of pneumococcal serotypes (valency) and the conjugate proteins used. The 7- (PCV-7) and 13-valent PCV (PCV-13) are conjugated to the non-toxic *C. diphtheria* CRM_197_ protein. In many affluent countries, PCV-13 has replaced PCV-7, while other countries use the 10-valent pneumococcal-*Haemophilus influenzae* Protein D conjugate vaccine (PHiD-CV). The PHiD-CV vaccine utilises *H. influenzae* protein D (PD) (for 8 serotypes), tetanus (serotype 18C) and diphtheria toxoid (19F) as its conjugating proteins (26, 27). PD is a highly-conserved outer membrane lipoprotein, which is immunogenic in both encapsulated (typeable) and non-typable *H. influenzae* (NTHi) species (28), although evidence of it inducing protection against these pathogens remains limited (29, 30).

All PCVs are highly effective and provide almost complete protection against invasive pneumococcal disease from vaccine-type serotypes (26). For our randomised controlled trial (RCT), we chose PHiD-CV instead of other PCVs for several important reasons. Firstly, in the same target population as our RCT, a 3-arm RCT (*n* = 227) demonstrated that PPV-23 given to pregnant First Nations women (compared with controls) did not reduce ear disease or nasopharyngeal pneumococcal carriage (31). Likewise, seven RCTs in other population groups using PPV-23 in the third trimester did not reduce pneumococcal infections and/or nasopharyngeal (i.e., upper airways) carriage in infants (14, 31). The non-efficacy of PPV-23 is not surprising as it is an inferior vaccine to PCVs being T-cell independent and thus inducing primarily IgM responses with little isotype switching to IgG or IgA antibodies and is unable to initiate immunological memory (14), which is consistent with clinical findings (23).

Secondly, PCVs that use CRM_197_ as the conjugating protein have been associated with hyporesponsiveness or immune tolerance to vaccine antigens (32, 33). The sole maternal immunisation RCT using a PCV found that infants of mothers randomised to a 9-valent prototype PCV had significantly reduced antibody responses to six PCV serotypes and increased ear disease at 6-months (32). As the conjugate protein for PCV-9 is the same as PCV-7 and PCV-13 [but different to PHiD-CV (26)], using PCV-13 may lead to comparable adverse events. Furthermore, hyporesponsiveness to PCV-7 was found in infants with prior natural infections and carriage of vaccine type strains (33). As First Nations infants have early onset and very high rates of pneumococcal carriage and ear infections (34), using PCV-13 for maternal immunisation may further increase the risk of these adverse events.

Thirdly, compared to other PCVs, PHiD-CV may provide additional *H. influenzae* protection for preventing infant ALRI (28). Mice immunised with PD (conjugating protein in PHiD-CV) had significant protection against *H. influenzae* lung infection and otitis media (28). *H. influenzae* are important pathogens in child and adult ALRIs (35, 36) and chronic lung diseases (37, 38). A systematic review (36) and a study employing transthoracic needle lung aspirations (35) described *H. influenzae* (mostly NTHi) as being second only to pneumococci as the most common cause of pneumonia in children from LMICs.

Fourthly, although maternal PHiD-CV might therefore be more beneficial and cost-effective (24) than PCV-13 at reducing infant ALRIs, there are currently no maternal immunisation studies using PHiD-CV.

In addition to the above, in First Nations children living in the Northern Territory of Australia, *H. influenzae* colonisation occurs early in infancy (34) and is an important cause of lower airway infections (35, 37). Further evidence of *H. influenzae* role in lower airway infections in children are: (a) *H. influenzae* is prevalent (30–85%) in the lower airways of children with bronchiectasis (38); (b) *H. influenzae* infection (most found to be were NTHi) in children with protracted bacteria bronchitis [a precursor of bronchiectasis (39, 40)] conferred >7-times higher risk of future bronchiectasis at the 2 year follow-up [hazard ratio (HR) = 7.6, 95% CI 1.7, 34.3] compared when *H. influenzae* was absent (41) and at the 5 year follow-up (Odds Ratio_adjusted_ = 5.1, 95%CI 1.4–19.1) (42); (c) PHiD-CV vaccination improved NTHi-specific cell- and antibody-mediated immune responses in children with bronchiectasis (25) and; (d) vaccination with PHiD-CV was associated with a significant reduction of NTHi infection in the lower airways of children (43).

In the context of the above, our RCT's primary aim is to determine whether vaccinating pregnant women with PHiD-CV reduces ALRIs in their infants in the first year of life. Our primary hypothesis is that maternal PHiD-CV immunisation will reduce the incidence of ALRI episodes in their infant's first year of life, compared to those who did not receive the vaccine.

Our secondary aims are to evaluate the impact of maternal vaccination with PHiD-CV upon:

Time-to the-first infant ALRI event using different ALRI definitions;Adverse events;Nasopharyngeal carriage of pneumococcal vaccine-type serotypes and *H. influenzae* at birth, 6 and 12-months of age; andImmune responses [vaccine-type antibody responses (total IgG to both vaccine-type pneumococcal serotypes and PD) and cell-mediated (cytokines) immune responses to pneumococci, NTHi and PD] in a subset of infants.

## Methods and Analysis

### Design

We are undertaking a parallel, single-blinded multicentre RCT (with concealed 1:1 allocation) to determine the efficacy of maternal immunisation with PHiD-CV at reducing ALRIs in infants during their first year of life. We randomised the first participant on 14th January 2019 and we anticipate continuing recruitment until late 2023. We currently have four study centres and six recruiting hospital sites: one centre in Malaysia (Likas Hospital in Kota Kinabalu) and three in Australia [Darwin (Royal Darwin Hospital, Darwin Private Hospital and Palmerston Regional Hospital) in the Northern Territory; and Brisbane (Royal Brisbane and Women's Hospital, RBWH), and Logan city (Logan Hospital) in South-East Queensland]. Previously we had a fifth study centre in Toowoomba (regional Queensland) whereby a research nurse was stationed at an Aboriginal Medical service, but after a year of unsuccessful recruitment, we abandoned this centre. Pending recruitment numbers and remaining funds, other centres/hospital sites may be included in the future.

### Study Population

#### Inclusion Criteria

(i) Generally healthy women aged 17–40 years; (ii) singleton pregnancy between 27^+6^ and 34^+6^ weeks gestation at the time of randomisation, (iii) planned delivery at study hospitals with delivery suites (Likas Hospital, Royal Darwin Hospital, Darwin Private Hospital, RBWH and Logan Hospital), (iv) the infant will be identified as either First Nations peoples (Australian Aboriginal and Torres Strait Islanders or Maori and Pacific Islanders from migrant families to Australia) or Malaysian, (v) treating obstetrician/medical practitioner managing the pregnancy approves the participant's enrolment in the study, (vi) provision of written informed consent and willing and able to meet the protocol requirements, and (vii) not planning to move from the study area before the infant reaches 12-months of age.

#### Exclusion Criteria

(i) Contraindication or known sensitivity to PHiD-CV, (ii) immune deficiency or suppression (primary or secondary); (iii) receipt of any pneumococcal vaccine in the previous 2-years; (iv) history of severe allergy e.g., anaphylaxis; (v) previously enrolled or (vi) pre-existing illness considered as a high-risk pregnancy (Table 1), (vi) current (or within 90-days prior to receiving study vaccine) or planned (during the active study period) immunosuppressive therapy, including systemic corticosteroids (≥14-days exposure in a 30-day period); (vii) administration of immunoglobulins and/or blood products, with the exception of Rh Immune Globulin, within 90-days prior to receiving the study vaccine, or planned administration of such products during the study period; (viii) active participation in a clinical trial of another investigational drug/vaccine or interventional therapy, or (ix) other conditions that the investigators/treating physicians consider should be excluded from the trial to prevent potential harm/risk to the subject or may adversely affect study outcomes.

**Table 1 T1:** Definition of high-risk pregnancies.

**Maternal illnesses**
•Diabetes mellitus diagnosed prior to pregnancy OR if diagnosed during pregnancy the treating obstetrician considers the person's glycaemic control status warrants exclusion from the study.
•Hypertension (resting blood pressure ≥140/90) requiring antihypertensive therapy
•Heart disease diagnosed by a cardiologist
•Active and/or unstable autoimmune disease on medication
•Confirmed and documented chronic renal failure
•Serious neurological disease (including epilepsy requiring drug therapy)
•Psychiatric disorder on medication known to be teratogenic (other psychiatric conditions are discussed on a case-by-case basis with local obstetrician and central office^*^).
•Cirrhosis
•Deep vein thrombus (current or recent in pregnancy)
•Uncontrolled thyroid disease (subclinical hypothyroidism may be included)
•Pulmonary disease that is not controlled by medications and/or FEV_1_ <70% using ethnic corrected values
•Substance abuse – judged on a case-by-case basis and in consideration of what substance is involved and how this might impact upon study participation (including alcohol and tobacco use)
**Pregnancy-related conditions**
•Malaria during pregnancy
•RBC Isoimmunisation
•≥3 spontaneous abortions AND not given birth to a healthy infant previously
•Previous stillbirth or neonatal death AND not given birth to a healthy infant previously
•Previous infant with known genetic disorder (discussed on a case-by-case basis with central office^*^)
•Previous infant with a major congenital anomaly (discussed on a case-by-case basis with central office^*^)
•Multiple pregnancy
•Expected to give birth to an infant with a major congenital abnormality
•Delivery <37-weeks expected or highly likely - (discussed on a case-by-case basis with central office^*^). Examples may include short cervix, incompetent cervix, past-history of spontaneous pre-term birth.
•Polyhydramnios (defined as either a deep vertical pocket >8cm or an amniotic fluid index >24cm on ultrasound examination) or oligohydramnios (defined as a maximum vertical pocket <2cm or amniotic fluid index <5cm on ultrasound examination)
•Intrauterine growth restriction or foetal growth restriction (<10th percentile) or macrosomia (>97th percentile for ethnicity)
•Preterm rupture of the membranes has occurred by the time of screening/enrolment
•Pre-eclampsia

* *Central office refers to the lead investigator ([name])*.

### Study Protocol

Pregnant women potentially eligible for the study are approached during a routine antenatal visit. Information is provided and on follow-up, they are invited to participate in the RCT. After confirming eligibility and providing informed consent, enrolled pregnant women are randomised to one of the two arms (intervention or control), as summarised in the Figure 1.

**Figure 1 F1:**
[figure not shown]
Overall schematic study design of our randomised controlled trial (RCT). *In a subset of infants, specimen collection includes nasopharyngeal swab (NPS) and infant blood (for immunoglobulins and peripheral blood mononuclear cells). PHiD-CV, 10-valent pneumococcal conjugate *Haemophilus influenzae* (Hi) Protein D vaccine.

#### Intervention and Control

Women randomised to the intervention arm receive a single dose of PHiD-CV (Synflorix®, GSK Biologicals, Belgium) between 27^+6^ and 34^+6^ weeks gestation. Those randomised to the control arm receive usual care (no PHiD-CV). If not already administered, seasonal influenza and dTPa vaccines are also offered at the same time to all women in both study arms as part of standard care.

#### Randomisation, Allocation Concealment and Blinding

At enrolment, participants are randomised to one of the two study arms (intervention or control). The random treatment allocation is computer-generated, stratified by site, using permuted blocks sizes of various sizes, concealed and supervised by a statistician.

Participants and study teams are unaware of the treatment to be allocated before the patients are entered into the study. The study is not placebo-controlled, but assessors collecting study outcome data are blinded to treatment allocation.

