### Primary Outcome

The main effects of the intervention will be determined by comparing the primary outcome of medically-attended ALRI rates in the first year of life recorded between the two groups (PHiD-CV vs. controls). We will report the incidence rate ratio (IRR) using negative binomial regression as well as the absolute difference between groups (with corresponding 95% CIs).

Sensitivity analyses for the primary outcome will be performed based upon the ALRI classification (described above). Also, we plan a preliminary analysis when the primary outcome for 50% of the sample size participants is available and each provides at least 6-months of individual data. We plan using 6-months of data (rather than 12-months, which is the time point for our RCT's outcome) for safety reasons, based on adverse events found in the prototype PCV-9 RCT (32).

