### For Secondary Aims

We will compare the inter-group proportion of children with any hospitalised ALRI, clinical pneumonia and radiographically-confirmed pneumonia using ORs with logistic regression (and 95%CIs). In addition, we will construct a Kaplan-Meier curve for each group for time-to-first ALRI episode and respiratory-related hospitalisation, perform a log-rank test and report a HR (using the Cox regression model).

For the secondary laboratory-based aims, we will compare between-group differences for: (i) IgG geometric means against PD (25) and serotype-specific pneumococci (31) using Student's T-test after logarithmic transforming the data (+/- maternal pre-vaccine levels adjustment); (ii) cytokine levels expressed by PBMCs after stimulation by live NTHi and pneumococci [Mann-Whitney (25, 51)]; and (iii) proportions of nasopharyngeal cultures positive for *H. influenzae* and pneumococci (vaccine and non-vaccine types) using Chi^2^ tests and reporting ORs (95%CIs) (44, 45).

The proportion of participants (pregnant participant and infants) with any adverse events will be compared between groups, using Chi^2^ tests and reporting ORs (95%CIs) (44, 45).

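### Allocation is stratified by site, but the named secondary tests have no site term, the primary model names no covariate, and baseline adjustment of IgG is left optional

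*Protocol article*

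**What the plan says.** Under Randomisation, Allocation Concealment and Blinding, the article states: "The random treatment allocation is computer-generated, stratified by site", with permuted blocks of varying size. The Design section adds "We currently have four study centres and six recruiting hospital sites" and does not say which of the two levels is the stratum.

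For the primary outcome, "We will report the incidence rate ratio (IRR) using negative binomial regression as well as the absolute difference between groups". No covariate is named, and the model is not called unadjusted either.

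Under For Secondary Aims:
- Time to first event: the plan is to "perform a log-rank test and report a HR (using the Cox regression model". No strata are mentioned.
- Hospitalised ALRI, clinical pneumonia and radiographic pneumonia: logistic regression with odds ratios, no covariates named.
- Carriage and adverse events: Chi-squared tests with odds ratios.
- Log IgG: Student's t-test, with a plus-or-minus sign before "maternal pre-vaccine levels adjustment".
- Cytokines: Mann-Whitney test.

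The section on data monitoring and analyses announces a detailed statistical analysis plan before the final analysis.

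**The concern.** Stratified blocks balance site across the arms. If site also predicts the outcome, an analysis that ignores it counts between-site differences as random noise although the design has removed most of them from the comparison. The standard error is then too large and the test conservative.

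Site is plausibly prognostic. The centres are in Kota Kinabalu, Darwin, Brisbane and Logan. Table 2 gives PCV-13 at 2, 4, 6 and 12 months for First Nations infants, at 2, 4 and 12 months for Maori and Pacific Island infants, and at 2, 4 and 6 months in Sabah. These differences bear on IgG and carriage at 6 and 12 months. The article also reports ALRI incidence well below what was predicted, so precision matters.

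The IgG option is a separate matter. The text names two analyses and selects neither. Maternal baseline blood is collected and maternal baseline IgG is a listed measurement, so the choice could be fixed now. Left open, it recurs for each serotype and for protein D at each sampling time, in about 35 infants per arm.

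**Working it through.** **Inputs from the Sample Size section:** 133 infants per group, 3 versus 2.1 ALRIs per infant-year (IRR 0.7), shape parameter 0.46, power 88%. Two-sided 5% is assumed because that section gives no significance level.

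**Reproducing the stated power, no site term**
- Variance of log IRR = (1/3 + 1/2.1 + 2 × 0.46)/133 = 1.7295/133 = 0.0130, so SE = 0.114.
- |log 0.7| = 0.3567, and 0.3567/0.114 − 1.96 = 1.17, so power = 87.9%.
- Pooled null variance gives 88.1%. Reading the dispersion as 1/0.46 gives 44.1%, so the plan used 0.46 as the dispersion.

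**Adding site.** The documents give no between-site variation, so a coefficient of variation c of the site rates is assumed. With 0.46 held as the overall dispersion, the within-site dispersion is k = (0.46 − c²)/(1 + c²), which replaces 0.46 in the variance. At c = 0.25, for example, k = 0.3975/1.0625 = 0.374, and the interval-width ratio is √[(0.8095 + 0.748)/1.7295] = 0.95.

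This was checked by simulation: four sites of about equal size, blocks of 4, maximum-likelihood negative binomial fits with and without site, 3,000 runs per scenario. Site rates were evenly spaced at 1 ± 0.447c and 1 ± 1.342c times the mean, so the highest-to-lowest ratio is (1 + 1.342c)/(1 − 1.342c).

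| c | Highest/lowest site rate | Within-site k | Interval width, with/without site | Power with site (formula) | Type I error without / with site (simulated) | Power without / with site (simulated) |
|---|---|---|---|---|---|---|
| 0 | 1.0 | 0.46 | 1.00 | 87.9% | 4.9% / 5.1% | 87.4% / 87.7% |
| 0.10 | 1.3 | 0.446 | 0.99 | 88.4% | 5.0% / 5.4% | 88.3% / 88.8% |
| 0.25 | 2.0 | 0.374 | 0.95 | 90.9% | 4.5% / 5.5% | 88.6% / 90.8% |
| 0.50 | 5.1 | 0.168 | 0.81 | 97.0% | 1.7% / 5.0% | 91.8% / 96.8% |

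The Monte Carlo error of a 5% rate is √(0.05 × 0.95/3000) = 0.4 points, so 4.5% at c = 0.25 is not clearly below nominal. The 1.7% at c = 0.50 is: there the unadjusted model SE averages 0.110 under the null, against a true SD of 0.090.

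**Log IgG.** ANCOVA on a baseline correlated r with the outcome multiplies the interval width by √(1 − r²):
- r = 0.3: √0.91 = 0.95
- r = 0.5: √0.75 = 0.87
- r = 0.7: √0.51 = 0.71

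The variance factor 1 − r² makes 70 infants perform like 70/0.75 = 93 at r = 0.5 and 70/0.51 = 137 at r = 0.7. The documents give no value of r. It is probably lower at 6 and 12 months, after the infants' own PCV-13 doses.

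**The case against.** The strongest reply is that covariate lists belong in the statistical analysis plan, which the article announces. Negative binomial, logistic and Cox models can all take a site term, and silence about covariates is not a statement that there are none. This stands for those three models. A reader might infer that every planned analysis is unadjusted, but the text does not say so, and it allows adjustment for IgG. The reply does not cover the t-test, Chi-squared and plain log-rank tests, which carry no site term as named, or the IgG option, which is stated text.

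A second reply is that site may matter little. The Sample Size section cites 3 ALRIs per year for both Northern Territory communities and an outer-Brisbane cohort, and gives no Malaysian rate. This stands too: the size of the gain is unknown and could be nil.

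A reader might also infer that power falls below 88%. That requires 0.46 to be a within-site value, which the article does not say. On that reading, site rates in the ratio 1.5 : 1.2 : 0.8 : 0.5 (coefficient of variation 0.38) gave simulated power of 83.8% without site and 87.1% with it. If 0.46 is the overall dispersion, omitting site only forgoes a gain.

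Nor does the omission raise false positives; the error is on the conservative side. For odds ratios and hazard ratios, adjustment changes the estimand because these measures are non-collapsible, and the interval need not narrow. The width argument applies to the IRR and the log-IgG difference.

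**Conclusion.** The point holds as a low-cost improvement to the analysis; it does not show an error in the sample size. The firmest part is the optional IgG adjustment, which lets the result be chosen after the data are seen, whatever the correlation turns out to be. Next is the mismatch between site-stratified allocation and named tests that carry no site term. For the primary model, the point is only that site should be named.

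The gain on the IRR rests on an assumed between-site variation and on 0.46 being the overall dispersion. It is practically nil for a coefficient of variation up to 0.10. At 0.25 the interval is about 5% narrower. At 0.50, roughly a fivefold range of site rates, it is about 19% narrower, and the unadjusted type I error falls to about 1.7%. The gain on log IgG likewise rests on an assumed correlation.

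**What to change.** Before unblinding, fix the following in the statistical analysis plan:
- **IgG:** replace the t-test with optional adjustment by one ANCOVA of log IgG on treatment, log maternal baseline IgG and site.
- **Primary outcome:** include randomisation site in the negative binomial model.
- **Time to event:** use a log-rank test and Cox model stratified by site.
- **Binary comparisons:** use Mantel-Haenszel tests and odds ratios stratified by site, and state that these are conditional on site.
- **Cytokines:** a site-stratified rank test is the counterpart to the Mann-Whitney test.
- **Definition of site:** state whether the stratum is the centre or the hospital, and use the level in the randomisation list.
- **Unadjusted results:** report them as supportive.

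The cost is wording and a few model terms. Site and maternal baseline IgG are already part of the planned data.
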